## Abstract

**Background:**

Urinary tract infections [UTIs] are very common in people with Spinal Cord Injury [SCI]. UTIs are increasingly difficult and expensive to treat as the organisms that cause them become more antibiotic resistant. Among the SCI population, there is a high rate of multi-resistant organism [MRO] colonisation. Non-antibiotic prevention strategies are needed to prevent UTI without increasing resistance. Probiotics have been reported to be beneficial in preventing UTIs in post-menopausal women in several *in vivo* and *in vitro* studies. The main aim of this study is to determine whether probiotic therapy with combinations of Lactobacillus reuteri RC-14 + Lactobacillus rhamnosus GR-1 [RC14-GR1] and/or Lactobacillus rhamnosus GG + Bifidobacterium BB-12 [LGG-BB12] are effective in preventing UTI in people with SCI compared to placebo.

**Method:**

This is a multi-site randomised double-blind double-dummy placebo-controlled factorial design study conducted in New South Wales, Australia. All participants have a neurogenic bladder as a result of spinal injury. Recruitment started in April 2011.

Participants are randomised to one of four arms, designed for factorial analysis of LGG-BB12 and/or RC14-GR1 v Placebo. This involves 24 weeks of daily oral treatment with RC14-GR1 + LGG-BB12, RC14-GR1 + placebo, LGG-BB12 + placebo or two placebo capsules. Randomisation is stratified by bladder management type and inpatient status. Participants are assessed at baseline, three months and six months for Short Form Health Survey [SF-36], microbiological swabs of rectum, nose and groin; urine culture and urinary catheters for subjects with indwelling catheters. A bowel questionnaire is administered at baseline and three months to assess effect of probiotics on bowel function.

The primary outcome is time from randomisation to occurrence of symptomatic UTI. The secondary outcomes are change of MRO status and bowel function, quality of life and cost-effectiveness of probiotics in persons with SCI. The primary outcome will be analysed using survival analysis of factorial groups, with Cox regression modelling to test the effect of each treatment while allowing for the other, assuming no interaction effect. Hazard ratios and Kaplan-Meier survival curves will be used to summarise results.

**Discussion:**

If these probiotics are shown to be effective in preventing UTI and MRO colonisation, they would be a very attractive alternative for UTI prophylaxis and for combating the increasing rate of antibiotic resistance after SCI.

**Trial registration:**

Australian New Zealand Clinical Trials Registry [ACTRN 12610000512022]. Date of registration: 21 June 2010.

**Electronic supplementary material:**

The online version of this article (doi:10.1186/s12894-016-0136-8) contains supplementary material, which is available to authorized users.

## Background

Urinary tract infections [UTIs] are very common in people with a neurogenic bladder. People with a spinal cord injury [SCI] and people with the spinal demyelinating form of Multiple Sclerosis [MS] are highly susceptible to the development of neurogenic bladder dysfunction.

UTIs have a high societal cost and current prevention strategies do not work. People with neurogenic bladder are at significant risk from UTI with approximately two [2] UTI episodes per year on average for persons with SCI [1]. One of the major clinical challenges for SCI patients and clinicians is that when patients get a UTI, simple oral antibiotics frequently are ineffective due to the high numbers of multi-resistant-organism [s] [MROs] within SCI populations [about 40–50 % of SCI people] [1, 2]. This greatly amplifies the health, societal and economic consequences of disease and can even lead to life threatening clinical problems that can spread if not controlled through hospitals and the community. Health care costs associated with cross infection are estimated at US$18–30 billion yearly in the USA and UK combined. Australian costs are expected to be proportionate [3]. Furthermore, based on the existing SCI UTI prevention literature, we have demonstrated that current commonly used methods of non-antibiotic UTI prevention in SCI do not work [4]. The prevention of UTI, particularly the more difficult to treat MRO UTI, is therefore a clinical imperative for those people with SCI and neurogenic bladder. Non-antibiotic prevention is needed to prevent UTI without increasing the antimicrobial resistance burden [5].

Probiotics are defined as a preparation containing viable, defined micro-organisms in sufficient numbers, which alter the microflora [by implantation or colonization] in a compartment of the host and thus exert beneficial health effects in this host [6]. Reid postulated that probiotics could reduce antibiotic related superinfections, disrupt bacterial biofilms, and enhance generalised mucosal immunity in the gastrointestinal and genitourinary systems [7]. In a systematic review conducted by Falagas et al., it was concluded that several probiotics tested, e.g. Lactobacillus rhamnosus GR-1 and Lactobacillus fermentum RC-14, delivered either intravaginally or orally, were efficacious in restoring vaginal flora and in preventing recurrent UTIs in women [8]. In another trial, Manley et al. demonstrated clearance of vancomycin-related enterococci in stool after treatment with Lactobacillus rhamnosus GG [9].

There are currently no known trials of oral probiotics and its efficacy in prevention of UTIs in people with neurogenic bladders. Darouiche and others have conducted more invasive trials involving inoculating neurogenic bladders with benign strains of Escherichia coli and showed this approach was effective at lowering the rate of UTIs per year [10–12].

### Study aims

#### Primary aim

To test the effectiveness of combination oral probiotic therapy Lactobacillus reuteri RC-14 + Lactobacillus rhamnosus GR-1 [RC14-GR1 capsules] and/or Lactobacillus rhamnosus GG + Bifidobacterium BB-12 [LGG-BB12 capsules] in preventing UTI in people with SCI compared to placebo.

#### Secondary aims

To examine whether probiotics may change or prevent colonisation or infection with MROs in persons with SCI.To examine the effects of probiotics on bowel function in persons with SCIExamination of indwelling and suprapubic catheters to determine:How probiotic intervention affects microbial community composition in the urine and urinary catheter.Differences between microbial communities in individuals who are symptomatic versus asymptomatic for UTI.To estimate the cost-effectiveness of probiotics in persons with SCI

A randomised controlled trial [RCT] was selected as the design most likely to provide a definitive conclusion to the primary aim.

## Methods/design

This is a prospective multi-site randomised, double-blind, double-dummy, placebo-controlled factorial design trial conducted in the state of New South Wales [NSW] Australia, in order to test the effectiveness of two probiotic therapies in preventing UTI in people with SCI. Participants will be recruited from the NSW SCI community and all the specialist SCI units in NSW hospitals, including their regional and rural affiliations. These units are located at the Prince of Wales Hospital [POWH], Royal Rehabilitation Centre Sydney [RRCS] and Royal North Shore Hospital [RNSH].

### Ethics approval

A multi-site ethics approval was obtained from the Human Research Ethics Committee [HREC] at each of the three SCI units in NSW, Australia. HREC Protocol no: 1008-282-CTN-GG [POWH SSA 1008-282 CTN, RR SSA 11/SSA03, RNSH SSA10/HAWKE/171].

The protocol for catheter sampling and culture independent technique of bacterial community identification was categorised as a low-risk study with separate ethics approval obtained from the HREC at each site [POWH HREC ref no. 11/036, RNSH HREC/10/HARBR/102 and SSA/10/HAWKE/171].

The trial was registered with the Australian New Zealand Clinical Trials Registry [ACTRN 12610000512022] on 21 June 2010. Informed consent will be provided prior to recruitment and participation. Participant recruitment commenced in April 2011.

### Sample size

The trial uses a factorial design which allows the two probiotics to be compared with placebo simultaneously without inflating the sample size, on the assumption that they do not interact with each other. [Refer Table 1].

**Table 1 Tab1:** Study design for ProSCIUTTU

	LGG -BB12 (B) Active (186)	LGG -BB12 (b) Placebo (186)
GR1-RC14 (A) Active (186)	AB or Intervention A (93)	Ab or Intervention B (93)
GR1-RC14 (a) Placebo (186)	aB or Intervention C (93)	ab or Intervention D (93)

UTI prevention: In our previous RCT with the same study population [4], 45 % of participants had a symptomatic UTI within six months. To have 80 % power to detect [at 5 % two-sided significance level] a 30 % reduction in the treatment group requires a total sample size of 350. Allowing for a 5 % loss to follow-up a final sample size of 372 is required, 93 participants being randomly allocated to each of the four study groups.

MRO treatment: It is expected that approximately 40 % participants will be MRO-positive at enrolment. Assuming 5-10 % become MRO-negative in the control group, a 15–20 % reduction in MRO-positive colonisation rate with probiotics would be detectable as significant at the 5 % level, with 80 % power, with a sample size of 372.

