### Data analysis

All analyses of outcomes will be by intention to treat, apart from safety outcomes which will be according to actual treatment received. Primary and MRO outcomes will be analysed using survival analysis. Cox regression modelling will be performed to test the effect of each treatment while allowing for the other, assuming no interaction effect. Hazard ratios and Kaplan-Meier survival curves will be used to summarise results. The extremely high prevalence of MRO in SCI will also allow us to explore whether probiotics can treat [or prevent] MRO colonisation in this group.

A survey was sent out to selected co-authors for determining the strength of association of several variables in regards to UTI in the SCI population [pre hoc review]. Only variables which have strong or moderate association will be included in the analysis.

Biofilms will be analysed using a combination of RNA based meta-community sequencing, TRFLP fingerprinting and culture based methods.

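### The stated sample size of 350 gives about 74–75% power, not 80%, for a 30% reduction from 45%; effect, formula and N need to be reconciled

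*Protocol article*

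**What the plan says.** The Sample size section of the protocol article gives every input to the primary calculation. From an earlier trial in the same population, "45 % of participants had a symptomatic UTI within six months". The section then fixes the operating characteristics ("To have 80 % power to detect", "at 5 % two-sided significance level") and concludes that a 30% "reduction in the treatment group requires a total sample size of 350". A 5% allowance for loss to follow-up raises this to 372, with "93 participants being randomly allocated to each of the four study groups". Table 1 sets each probiotic against its placebo at the factorial margin, 186 v 186. The section also says that the factorial layout "allows the two probiotics to be compared with placebo simultaneously without inflating the sample size", on condition that the two products do not interact. The Data analysis section plans a Cox model to "test the effect of each treatment while allowing for the other, assuming no interaction effect". No sample size formula is named.

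**The concern.** Control risk, effect, test level, sidedness, power and allocation are all stated, so the total can be checked directly, and it comes out too small. This is the only power justification for the primary outcome. If the literal effect was intended, the planned type II error was about 25% rather than 20%, and the target against which recruitment is judged was set too low. If a different effect was intended, the article misreports the effect that the trial was designed to detect.

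**Working it through.** **Inputs (Sample size section, Table 1).** Control risk p1 = 0.45. A 30% relative reduction gives p2 = 0.45 × 0.70 = 0.315, a difference of 0.135 and a mean risk of 0.3825. Two-sided 5%: z = 1.960. 80% power: z = 0.842. Allocation is 1:1 at the margin, so 350 evaluable means 175 v 175.

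**1. Can 350 be reproduced from these inputs?**

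*Two proportions, pooled variance under the null.* n per group = [1.960 × √(2 × 0.3825 × 0.6175) + 0.842 × √(0.45 × 0.55 + 0.315 × 0.685)]² / 0.135² = (1.347 + 0.573)² / 0.018225 = 202.3. Total about 405.

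*Two proportions, unpooled.* n per group = (1.960 + 0.842)² × (0.2475 + 0.2158) / 0.018225 = 199.5. Total about 399.

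*Continuity-corrected.* Total about 434.

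*Log-rank or Cox, matching the planned analysis.* HR = ln(1 − 0.315) / ln(1 − 0.45) = ln 0.685 / ln 0.55 = 0.633.
- Schoenfeld: events = 4 × (1.960 + 0.842)² / (ln 0.633)² = 150; total = 150 / 0.3825 = 392.
- Freedman: events = (1.960 + 0.842)² × [(1 + 0.633) / (1 − 0.633)]² = 155.2; total = 155.2 / 0.3825 = 406.

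So the stated inputs need 392–406 (434 with continuity correction). The stated 350 is short by 42–56 participants, about 11–14% of the requirement.

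**2. Power at the stated sizes, 45% v 31.5%.**

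| Participants analysed | Two proportions (pooled) | Log-rank (Schoenfeld) |
|---|---|---|
| 350 | 74.0% | 75.4% (about 134 events) |
| 372, no loss | 76.6% | 77.9% (about 142 events) |

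A simulated log-rank test stratified by the other factor (3,000 runs, one active product) gave 75.6% at 350 and 77.7% at 372. At 350, 80% power is reached at a relative reduction of about 32% (79.6% by two proportions, 80.9% by log-rank).

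**3. Which other readings come near 350?**

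| Reading | Total N | Departure from the text |
|---|---|---|
| 45% v 30%, two-sided, continuity-corrected | 351 (352 in equal groups) | A reduction to 30%, i.e. 15/45 = 33% relative |
| 45% v 31.5%, one-sided, continuity-corrected | 348 | The text says two-sided |
| Freedman events divided by 45% for everyone | about 345–347 | Ignores the lower risk in the treated half |
| HR 0.70 | 624–639 | Not near 350 |
| 30-point absolute drop | 72 | Not near 350 |

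**4. Step to 372.** 350 / 0.95 = 368.4, i.e. 369. The published 372 covers this and divides by four, so the loss allowance is not the problem.

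**5. Sensitivity: both products active.** With HR 0.633 for each and no interaction on the hazard scale, the cell risks are 45%, 31.5%, 31.5% and 21.3%, and the margins are 38.25% v 26.4%. At 350 there are about 113 events, and power per probiotic is 66.1% (two proportions) or 68.2% (log-rank). If the effects instead add on the risk-difference scale, the margins are 38.25% v 24.75% and power is about 78%.

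**The case against.** The strongest reply is that 350 may be right and the described effect wrong. A reduction to 30%, with the common continuity correction, gives 351, and at 350 the uncorrected power for that contrast is about 83%. This has force: a small slip in wording would explain the figure, and the article names no formula. It means that one cannot assert that 350 is unreachable by any reading, or insist that 75% is the true design power. It does not remove the point, because the text gives a 30% reduction and a two-sided test, and on those terms 350 is too small by every standard formula tried.

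A reader might also infer that the claim of no sample size inflation is false because power falls when both probiotics work. The documents do not support that. The sentence is conditional on no interaction, it is the usual way to say that a 2×2 factorial answers two questions with one sample, and it promises nothing about power when both products are active. The 66–68% figure rests on an added scenario and on a constant hazard ratio; on an additive risk scale it is about 78%. It is a sensitivity result and not a contradiction.

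Finally, the Trial status section reports 207 recruited. No reader who sees this will assume that the planned power was reached: at 207 the same inputs give about 52–53%. That limits the practical effect of the error. It does not make 350 correct, since the recruitment shortfall is judged against the stated target.

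**Conclusion.** The point holds as a mismatch between stated inputs and stated result. For 45% v 31.5%, two-sided 5%, 80% power and 1:1 comparison at the margin, the requirement is 392–406 evaluable participants (434 with continuity correction), not 350. Power at 350 is about 74–75%, a shortfall of 5–6 points, and the loss allowance does not restore it. This rests on reading the 30% as a relative reduction and 45% as the risk without active treatment; the log-rank figures also assume proportional hazards. Confidence is high that the numbers do not agree. Which of them is at fault, the effect or the total, cannot be decided from the article.

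**What to change.** Keep the design, allocation and analysis. In the Sample size section, state the effect and the formula that were used, and make effect, formula and N agree:

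- If 45% v 31.5% was intended, say that 350 evaluable participants give about 75% power, or that the relative reduction detectable with 80% power is about 32%.
- If 45% v 30% was intended, correct the effect to a reduction to 30% (about one third) and name the continuity correction.

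Preferably also give the hazard ratio and expected events, so that the calculation matches the Cox analysis. For 45% v 31.5% these are HR 0.633 and about 134 events at 350, against about 150–155 needed for 80% power. A sentence on power when both products are active (about 66–68% per probiotic under a constant hazard ratio) is optional. The statement about not inflating the sample size need not be deleted.

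The cost is wording only, with a slightly less favourable stated power or effect.

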### Randomisation and blinding of assessors

A simple stratified [computer generated] randomisation protocol is used. JS is responsible for generating the allocation sequence. Randomisation is stratified by bladder management types [indwelling/suprapubic vs intermittent catheters vs condom drainage/reflex voiding] as well as inpatient/outpatient status. Randomisation occurs following participant’s compliance check at Day 4. One central pharmacy is responsible for the assignment and distribution of the intervention for the entire study. All four treatment regimens will be indistinguishable by appearance and taste, and all participants receive the same quantity of tablets. All clinical staff, researchers and participants remain blind to treatment allocation throughout this process. An audit of randomisation, product allocation and dispensing stock will be performed at the completion of the study by MT, who is not affiliated with the final analysis and the clinical management of the study or study participants.

### Participants

All participants are to be over 18 years of age and are required to provide written consent. All participants with known neurogenic bladder as a result of SCI who meet inclusion criteria and gave written consent are enrolled. BL, ST, SR, JK, LB, GW and CBR are responsible for enrolling participants.

Inclusion criteria:Had a known neurogenic bladder;Had a stable SCI or stable multiple sclerosis with a known spinal demyelinating lesion;Had a stable bladder management technique [i.e. not receiving bladder management education for at least 4 weeks] and using a bladder management technique such as indwelling catheter, suprapubic catheter, clean intermittent self-catheterisation or reflex/condom drainage;Agreed to fortnightly telephone consultation for themselves and their care team during the six month study period;Agreed not to take any other probiotic in addition to the allocated intervention during the course of the study. This includes all oral or topical preparations of yoghurt and urinary antiseptics [e.g. methenamine hippurate (hiprex) or cranberry preparations].

Exclusion criteria:Receiving bladder management education within the last 4 weeks;Being treated for, or symptomatic from a current infection or long-standing pressure sore;Known to have a complex bladder disturbance requiring surgical intervention e.g. known cystoplasty, renal or bladder calculus, significant hydronephrosis, or current pyelonephritis;Known to have chronic open wound/s or known long-standing osteomyelitis [greater than 6 weeks];On long-term antibiotic therapy for any indication;Known to have a history of adverse drug reaction to yoghurt products or a demonstrated intolerance to the probiotics used. Lactose intolerance was NOT an exclusion criterion;Known to have severe renal or hepatic failure;Requiring full [invasive] mechanical ventilation;Receiving immunosuppressant medications or have an underlying immunosuppressive disease [for example HIV or end-stage/ progressive diabetes mellitus, multiple sclerosis or cerebrovascular disease];Planning to have oral surgery during the intervention period;Concurrently enrolled in another intervention study [observational studies or inclusion following completion of another study was allowed].

Each participant is enrolled for a six month study period, which includes 24 weeks of treatment [see Fig. 1]. Each participant randomised is required to take two tablets orally each day consisting of either RC14-GR1 + LGG-BB12 or RC14-GR1 + placebo or LGG-BB12 + placebo or 2 placebo tablets.

**Fig 1 Fig1:**
[figure not shown]
Participant Study Flow Chart for ProSCIUTTU

Active Interventions:GR1-RC14. Concentration per capsule is 5.4 × 10^9^ colony forming units.LGG-BB12. Concentration per capsule is 7 × 10^9^ colony forming units.

Participants will be assessed at Day 0, 3 months and 6 months, supported by fortnightly phone calls to determine health status and confirm intercurrent symptomatic UTI status. [Fig. 1] Following witnessed informed consent, evaluations conducted will be:Intervention issues and compliance.Quality of life assessment with the Short Form Health Survey [SF-36] – baseline and 6 months plus study endpoint if reached.Microbiological swabs of rectum, nose and groin, urine culture and collection of urinary catheters for participants with indwelling or suprapubic catheters – baseline, 3 months and 6 months. Urine cultures also performed if at study endpoint. Specific instructions for sampling were given by study co-ordinator to research assistants and community nurses performing the swabs to ensure consistency.Bowel questionnaire [13, 14] - baseline and 3 months.

### Catheter-bioflora analysis

The indwelling urethral and suprapubic catheter biofilm is examined as a proxy for the urinary tract microbial community. Culture-independent techniques in profiling human microbes will be used to determine the composition of adherent microbes through the examination of the bacterial 16S rDNA gene by Terminal Restriction Fragment Length Polymorphism [TRFLP] [15] and via next-generation sequencing [16–19]

Samples are selected irrespective of interventional grouping.

Samples are also selected from groups with recurrent symptomatic UTI compared to no-UTI symptoms over the study follow-up period. All TRFLP and sequencing analysis will be conducted blinded by the use of a participant identification key that de-identifies the data.

TRFLP is done in collaboration with the Ramaciotti Centre for Genomics, University of New South Wales and sequencing through the Singapore Centre for Environmental Life Sciences Engineering at Nanyang Technological University, Singapore.

### Study endpoints

The primary outcome measure is the time from randomisation to occurrence of “symptomatic UTI” [Fig. 2]. The date of the endpoint is the date participants develop symptoms consistent with a “symptomatic UTI” as per the algorithm, not the date participants start developing any symptoms. Table 2 outlines the definition of “symptomatic UTI” as primary endpoint for ProSCIUTTU. For participants who do not experience a “symptomatic UTI”, the primary outcome is at six months. Participants who cease intervention early are followed up until the end of the study period.

